### *Muscle biopsies*

During the test day four muscle biopsies will be obtained. Four biopsies are necessary to be able to measure mixed muscle fractional synthetic rate in a post-absorptive as well as in the post-prandial state. Biopsies will be obtained from the middle region of the vastus lateralis muscle (15 cm above the patella) and approximately 2 cm below entry through the fascia by the percutaneous needle biopsy technique described by Bergström et al. (57), using a modified needle (Maastricht Instruments). With this instrument, better results are obtained for sample size, whereas subjects' discomfort is minimized. In short, skin and muscle fascia will be locally anesthetized using 2% xylocaine. After 10 minutes a small incision will be made in skin and fascia after which the biopsy needle will be introduced in the muscle. Vacuum will be applied to the needle and, with the needle kept *in situ*, several small muscle samples (total  $\pm$  50-80 mg) will be taken. Following the muscle biopsy, the skin will be closed using a Steristrip® and covered by Tegaderm® after which a pressure bandage will be applied (Acrylastic®).

The percutaneous needle biopsy technique was introduced within the Department of Human Movement Sciences by Profs. [name] and [name] more than 25 years ago. Since this introduction, the technique has been successfully used to perform numerous human *in vivo* studies focusing on skeletal muscle metabolism within the Department of Human Movement Sciences (for review see (58, 59)). In addition, recently approved MEC proposals continue to combine the use of continuous tracer infusion and muscle biopsy technique in young (MEC 09-3-080, MEC 09-3-054) and elderly men (MEC 07-3-086, MEC 09-3-080, MEC 09-3-054, MEC 09-3-078, MEC 10-3-065, MEC 10-3-80). Based on previous experience, discomfort for the subjects with the technique used in our laboratory is negligible.

## **6.4 Withdrawal of individual subjects**

Subjects can leave the study at any time for any reason if they wish to do so without any consequences. The investigator can decide to withdraw a subject from the study for urgent medical reasons.

## **6.5 Replacement of individual subjects after withdrawal**

New subjects will replace subjects that are withdrawn from the study.

**6.6 Follow-up of subjects withdrawn from treatment**

Subjects withdrawn from treatment will not be followed-up after eventually handing over responsibilities to medical personnel.

**6.7 Premature termination of the study**

In case the safety and wellbeing of the subject is in danger, or there are non-expected disadvantages of the participation for the subject, the subject will directly be excluded from the research. There are no risks connected to the premature termination of the study.

In case of premature termination or suspension of the trial for any reason, the investigator will inform:

- The regulatory authorities (MEC)
- The subject, assuring him or her appropriate treatment and follow up

## 7. SAFETY REPORTING

### 7.1 Section 10 WMO event

In accordance to section 10, subsection 1, of the WMO, the investigator will inform the subjects and the reviewing accredited METC if anything occurs, on the basis of which it appears that the disadvantages of participation may be significantly greater than was foreseen in the research proposal. The study will be suspended pending further review by the accredited METC, except insofar as suspension would jeopardise the subjects' health. The investigator will take care that all subjects are kept informed.

### 7.2 Adverse and serious adverse events

Adverse events are defined as any undesirable experience occurring to a subject during the study, whether or not considered related to the experimental treatment. All adverse events reported spontaneously by the subject or observed by the investigator or his staff will be recorded.

A serious adverse event is any untoward medical occurrence or effect that at any dose:

- results in death;
- is life threatening (at the time of the event);
- requires hospitalisation or prolongation of existing inpatients' hospitalisation;
- results in persistent or significant disability or incapacity;
- is a congenital anomaly or birth defect;
- is a new event of the trial likely to affect the safety of the subjects, such as an unexpected outcome of an adverse reaction, lack of efficacy of an IMP used for the treatment of a life threatening disease, major safety finding from a newly completed animal study, etc.

All SAEs will be reported through the web portal *ToetsingOnline* to the accredited METC that approved the protocol, within 15 days after the sponsor has first knowledge of the serious adverse reactions..

SAEs that result in death or are life threatening should be reported expedited. The expedited reporting will occur not later than 7 days after the responsible investigator has first knowledge of the adverse reaction. This is for a preliminary report with another 8 days for completion of the report.

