### 3. STUDY DESIGN

[figure not shown]

**Figure 1:** Flow diagram of study design.

The study will have a parallel design and will consist of a short-term (1 week) and long-term (12 weeks) dietary intervention period.

Two days before the baseline measurement, subjects will be fed in energy balance (EB) with protein intake of 15En%. After the baseline measurement, subjects (n=40) will be randomly divided in two groups (2 x n=20). The two applied conditions will differ in the absolute protein content of the meals, including 5En% and 30En% from protein. Fat content will be kept constant in all three conditions regarding the possible effects of fat intake on fat oxidation, resulting in macronutrient compositions of the diets of En% Protein/Carbohydrate/Fat: 5/60/35 and 30/35/35. Both conditions will be compared with the baseline measurement when subjects are fed in energy balance with a macronutrient composition of 15/50/35 En% (Protein/ Carbohydrate/Fat). During the 12 weeks dietary intervention period, subjects will receive recipes prescribed by a qualified dietician. The 30En% protein group will receive recipes for high-protein meals and in addition protein supplements. The 5En% protein group will receive recipes for low-proteins meals and in addition carbohydrate supplements.

To determine energy expenditure and substrate oxidation, subjects will stay in the respiration chamber for 48 hours at baseline, after 1 week and after 12 weeks of an energy balanced diet. During the stay in the chamber, polysomnography will be used to measure wake and sleep phases continuously, in order to determine sleep duration and sleep quality. Every morning blood samples will be taken in fasted state to determine plasma concentrations of glucose, insulin and free fatty acids. Appetite and mood profiles will be measured hourly and before and after each meal, by anchored 100mm visual analogue scales and by POMS and STAI-state questionnaires.

At the start and after 12 weeks, 3-compartment body composition will be determined with the deuterium dilution technique combined with densitometry (BodPod). To investigate fat distribution MRI and  $^1\text{H}$ -MRS will be used. Abdominal fat will be assessed at baseline, and liver fat and intramyocellular lipid (IMCL) content, as well as the mass of the vastus lateralis muscle will be measured at baseline and after 12 weeks.

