To assess dietary protein intake and thus compliance to the diet, subjects will complete 24-hour urine collections at the start, during their stays in the respiration chamber and at week 11. One week before the baseline measurement and at week 11 an accelerometer will be worn to measure habitual physical activity.

During the screening, after 6 weeks and after 12 weeks of high protein diet the glomerular filtration rate (GFR) will be estimated using the Modification of Diet in Renal Disease (MDRD) study equation (for detail see section 6.3).

After the final measurement in the respiration chamber the subjects are invited for a final test day in which (muscle) protein synthesis will be measured. This additional test day is not compulsory and subjects that do not want to participate can still take part in the rest of the study.

During the test day, subjects will receive a test-drink containing 20 g intrinsically labelled casein to be able to measure the effect of protein ingestion on muscle protein synthesis. This allows us to determine the true incorporation of amino acids from the ingested, intact casein into the muscle, taken into account the influence of digestion and absorption processes of a whole protein (24-27). Intrinsically labelled milk proteins were derived from milk that has been collected from cows that were infused with L-[1-C] phenylalanine (27). This procedure has been successfully used in human intervention studies by the research group of [name]. [name] (MEC 06-3-064, MEC 07-3-086, MEC 09-3-078.3, MEC 10-3-080), which has already resulted in multiple publications (24-27). Subsequently, plasma and muscle samples will be collected. Together with the use of an intravenous L-[ring-H5]phenylalanine, L-[1-C]-leucine and L-[ring-H2]tyrosine infusion, the digestion and absorption kinetics of the ingested protein, whole body protein balance and the fractional synthetic rate (FSR) of mixed muscle protein in the fasted and fed state in an *in vivo* human setting will be assessed.

[figure not shown]

**Figure 2:** time schedule of the additional test day.

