instructed on how to handle the bottles to reduce these risks. MRI and MRS are safe, non-invasive procedures with no ionizing radiation and these procedures do not expose the subjects to any risks if the exclusion criteria (no electronic implants, no pacemakers, no metal fragments in the eyes, skin or body) are well respected. Additionally, there are no risks for the subject in consuming any of the provided meals, because people with certain food allergies are excluded for participation and all food items will be commercially available in normal Dutch supermarkets. Studies in the respiratory chamber will be conducted using standard operating procedures. A pair of subjects will always participate in the study at the same time and therefore they will never be alone. The subjects will be able to contact the investigators during the entire night. In addition, they will be able to get out of the chamber at any time they feel uncomfortable. A 30En% protein or a 5En% protein diet for 12 weeks will not have any side effects on the subject's health.

This study does not have any benefits for the subjects themselves, but will give possible new knowledge for treatment of obesity.

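### Adverse events are recorded only if volunteered or seen by staff, and dated contact in mid-diet appears to differ by arm, which risks missed and possibly uneven recording

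*Protocol*

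**What the plan says.** Section 7.2 starts from a wide definition: "Adverse events are defined as any undesirable experience occurring to a subject during the study", whether or not related to treatment. It then sets the capture rule: "All adverse events reported spontaneously by the subject or observed by the investigator or his staff will be recorded". The protocol describes no scheduled question, diary or checklist for adverse events. The appetite, mood and anxiety scales completed in the respiration chamber are listed in section 6.1.2 as secondary endpoints, not as safety collection.

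Section 3 sets the contacts shared by both arms: "subjects will stay in the respiration chamber for 48 hours at baseline, after 1 week and after 12 weeks of an energy balanced diet", and "subjects will complete 24-hour urine collections at the start, during their stays in the respiration chamber and at week 11". An accelerometer is also worn at week 11. Kidney function is handled differently: "after 6 weeks and after 12 weeks of high protein diet the glomerular filtration rate (GFR) will be estimated". For the time at home, "During the 12 weeks dietary intervention period, subjects will receive recipes prescribed by a qualified dietician", plus supplements. Neither the timing nor the form of dietician contact is given for either arm.

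Section 9.3 says of the diets: "A 30En% protein or a 5En% protein diet for 12 weeks will not have any side effects".

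**The concern.** Under a passive rule, the chance that a mild or passing complaint is recorded depends on how often the subject has an easy occasion to mention it. If one arm has a dated contact halfway through the diet and the other does not, that chance may differ by arm for reasons unrelated to the diets.

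Two things are at stake. The first is detection. Section 7.1 (informing the ethics committee when disadvantages exceed what was foreseen) and section 6.7 (removing a subject for unexpected disadvantages) both depend on the investigator hearing about problems. Section 6.6 adds that subjects withdrawn from treatment are not followed up, so a subject who stops at home because of a complaint may never be asked about it. The second is interpretation. A low event count collected this way would give little support to the section 9.3 statement on side effects, and an informal comparison of the arms could reflect contact as well as diet.

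**Working it through.** The protocol states no figure for adverse events, so the check is to list the dated procedures after the diet starts and measure the gaps.

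**Inputs (section 3)**
- Both arms: chamber stays at weeks 1 and 12; urine collection and accelerometer at week 11.
- 30En% arm, as worded: kidney-function estimate at weeks 6 and 12.

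**Gap = week of next dated procedure − week of previous one**
- 5En% arm (weeks 1, 11, 12): 11 − 1 = 10; 12 − 11 = 1. Longest gap 10 weeks.
- 30En% arm (weeks 1, 6, 11, 12): 6 − 1 = 5; 11 − 6 = 5; 12 − 11 = 1. Longest gap 5 weeks.

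The week-11 procedures are done in daily life and the protocol does not say that staff meet the subject then. Without week 11, the longest gaps are 12 − 1 = 11 weeks and 12 − 6 = 6 weeks. The difference between arms is 5 weeks either way.

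**Is the week-6 contact certain?** Three sections bear on it:
- Section 3 dates it and ties it to the high-protein diet.
- Section 6.3.2 (blood samples) gives a total of 174 mL per subject. This reproduces as 3 × 10 + 18 × 8 = 30 + 144 = 174 mL, with no kidney-function sample in it. The 10 mL screening sample, which is clearly planned in sections 4.1 and 6.3.1, is not in it either, so the total is weak evidence that no week-6 sample is taken.
- Section 9.3 limits venepuncture to one sample at screening and one per chamber day. Week 6 is neither, so this conflicts directly with section 3.

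**The possible readings, using week 11 as a contact**

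| Week-6 sample | Longest gap, 5En% | Longest gap, 30En% | Is anyone asked about events? |
|---|---|---|---|
| 30En% arm only | 10 weeks | 5 weeks | No |
| Neither arm | 10 weeks | 10 weeks | No |
| Both arms | 5 weeks | 5 weeks | No |

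The imbalance appears only on the first reading. The passive rule is present on all three.

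**The case against.** The case on the other side has real weight.

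- Spontaneous reporting needs no visit, and both arms can mention earlier complaints at weeks 11 and 12. If subjects recall and mention complaints up to 10 weeks old, the extra contact makes no difference.
- The extra contact is described only as a kidney-function estimate. No adverse-event question is attached to it, so a complaint still has to be volunteered there.
- Dietician contact is undated but described for both arms, and the flow diagram is not available. Week 6 is therefore the only *dated* mid-period procedure in the readable text, and perhaps not the only contact.
- Adverse events are not an endpoint in section 6.1, and section 8 plans no comparison of them between arms. The section 9.3 sentence is an advance risk statement, not a hypothesis to be tested.

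All of this stands, and it limits the conclusion. A reader might infer that events on the 5En% diet are under-recorded, or that the arms cannot be compared for safety. The documents support neither. Nor do they give an event rate or a probability of reporting, so any count of missed events would rest wholly on invented inputs; none is offered here.

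What the objection does not remove is the rule itself. Section 7.2 states a method, so this is not a detail left for a statistical analysis plan, and the method leaves up to 10 weeks at home in which nobody is due to ask.

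**Conclusion.** The point holds as a risk, not as a demonstrated bias. Passive capture creates a risk of missing events during the home-diet period on every reading of the week-6 contact. On the wording of section 3 there is also a possible risk of differential recording, because the longest gap between dated procedures is about 10 weeks on 5En% and 5 weeks on 30En%. The second part assumes that section 3 governs over section 9.3, that dietician contact does not fill the gap, and that some complaints fade from memory before week 11. The primary endpoints and the sample size are not affected. This is a low-cost improvement to safety ascertainment, not a flaw that undermines the trial.

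**What to change.** Amend section 7.2 so that, in addition to spontaneous reports and staff observation, staff ask every subject in both arms the same open, non-leading question (for example, whether there have been any health problems since the last contact) at the same times: baseline, week 1, week 6 by a short call or message, and week 11/12. Report events by randomised arm over these common windows, unless a statistical analysis plan already provides for this.

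Reconcile sections 3, 6.3.2 and 9.3 on who is sampled at week 6. A dated contact in one arm only also sits awkwardly with the double-blind design stated in section 6.2.

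The cost is a sentence in section 7.2, a line on the case record and a call of a few minutes at week 6 for subjects not otherwise seen then. The other questions use existing contacts. The downside is that more minor events will be recorded.

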### **7.3 Follow-up of adverse events**

All adverse events will be followed until they have abated, or until a stable situation has been reached. Depending on the event, follow up may require additional tests or medical procedures as indicated, and/or referral to the general physician or a medical specialist.

## **8. STATISTICAL ANALYSIS**

### **8.1 Descriptive statistics**

All the data will be collected and kept in Microsoft Excel. Means and standard error of the mean (36) will be calculated and plotted in either bar or line graphs (when appropriate).

### **8.2 Univariate analysis**

The Statistical Package for the Social Sciences (SPSS) will be used to perform univariate analyses. Differences in energy expenditure, substrate oxidation, (muscle) protein synthesis and sleep between the two conditions (and baseline measurement) will be tested with one-way ANOVA with Bonferroni post hoc corrections. Changes in VAS ratings over time between and within groups will be tested with repeated-measures ANOVA with Bonferroni post hoc corrections. Multiple linear regression analyses will be performed to determine between subjects effects. All statistical tests will be two-sided and differences will be considered statistical significant if  $p < .05$ .

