The present study aims to determine energy expenditure, substrate oxidation and muscle protein synthesis rates with diets contrasting in protein content over a longer period of time. By determining the long-term effect of high protein and low protein diets it will be possible to elucidate if the effect of protein on energy expenditure is a permanent or transient effect, as well as the contribution of protein synthesis to the protein induced thermogenesis. Moreover, the study aims to determine the different effects of diets contrasting in protein content on sleep duration and sleep quality, measured by electroencephalography. We hypothesize that the diet with 30En% of protein will affect sleep, energy expenditure and will have a fat free mass sparing effect by increasing protein synthesis. The diet with 5En% of protein will not affect sleep, energy expenditure and will not spare fat free mass. By comparing subjects with different sleep duration and quality, it will be possible to confirm the fat free mass sparing effect of sleep.

As a secondary aim the present study determines body composition (including body fat content, fat mass and fat free mass), body fat distribution (including abdominal, liver and muscle fat) and (muscle) protein synthesis in response to diets contrasting in protein content.

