### **8.3 Multivariate analysis**

Multiple linear regression analyses will be performed to determine the independent contribution of gender, age and BMI on energy expenditure, substrate oxidation, (muscle) protein synthesis and sleep. All statistical tests will be two-sided and differences will be considered statistical significant if  $p < .05$ .

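### Section 8.2 treats the subjects' own baseline as a separate group in a one-way ANOVA of the main outcomes, and no planned test formally compares week 12 with week 1 between diets

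*Protocol*

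**What the plan says.** Protocol section 8.2 assigns four outcomes (energy expenditure, substrate oxidation, muscle protein synthesis and sleep) to a single method. Differences "between the two conditions (and baseline measurement) will be tested with one-way ANOVA with Bonferroni post hoc corrections". The following sentence gives a different method to a secondary outcome: "Changes in VAS ratings over time between and within groups will be tested with repeated-measures ANOVA with Bonferroni post hoc corrections".

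Section 3 has all 40 subjects measured at baseline and only then randomised, 20 to each diet. It makes baseline a planned comparator: "Both conditions will be compared with the baseline measurement when subjects are fed in energy balance". Chamber stays take place at baseline, after 1 week and after 12 weeks, in the same subjects.

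Section 1 states the purpose of the longer follow-up: "it will be possible to elucidate if the effect of protein on energy expenditure is a permanent or transient effect".

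Two regressions are planned. The one in section 8.2 concerns between-subject effects, with no covariates listed. The one in section 8.3 addresses "the independent contribution of gender, age and BMI on energy expenditure" and the other main outcomes.

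**The concern.** A one-way ANOVA assumes that the observations in its cells are independent. Here the baseline cell and the diet cells hold the same people. The diet-versus-baseline contrasts are therefore judged against between-subject variance, although they are within-subject differences. The comparison between diets does involve different people, but it makes no use of the baseline chamber value that every subject already has.

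The second gap is the time question. The design pays for two chamber stays on diet so that a lasting effect can be told from a passing one. For energy expenditure, substrate oxidation and sleep, however, no test in section 8 contrasts week 12 with week 1 between the diets. The answer would have to come from setting two separate significance results side by side, which is not a test of change.

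At stake are avoidable losses of power on the primary outcomes and an unsupported reading of a headline aim.

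**Working it through.** **Inputs.** From section 4.4: 14.6 ± 2.9 and 10.5 ± 3.8, alpha 0.05, power 0.90, 16 per group, 20 after dropout. From section 8.2: two-sided tests with Bonferroni correction. Three cells give three pairwise contrasts, so the level is 0.05/3 = 0.0167. Assumed, because the protocol gives neither: the within-subject correlation ρ, shown from 0.5 to 0.9, and equal variances across cells. Section 8.2 does not say which visit enters the ANOVA or how the baselines are grouped. The layout used here is all baselines in one cell and the two diets at one visit.

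**The plan's own figure.** d = (14.6 − 10.5)/√((2.9² + 3.8²)/2) = 1.213. Exact two-sided t-test power is 0.894 at 15 per group and 0.913 at 16, so 16 is reproduced, and 16/(1 − 0.2) = 20. The sample size therefore rests on a plain two-group comparison at 0.05, with no baseline or time term.

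**Diet versus baseline.** With n per arm and 2n baselines, the ANOVA assumes a variance of σ²(1/n + 1/(2n)). Each arm supplies half of the baselines, so the true variance is σ²(1/n + 1/(2n) − ρ/n). The ratio is 1 − 2ρ/3. The error rates and powers below come from 20,000 simulated trials per setting at 16 per arm; the power is for an illustrative shift of 0.5 SD at level 0.0167.

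| ρ | true/assumed variance | actual error (nominal 1.67%) | power, one-way ANOVA | power, paired test |
|---|---|---|---|---|
| 0.5 | 67% | 0.37% | 17% | 28% |
| 0.7 | 53% | 0.11% | 15% | 47% |
| 0.8 | 47% | 0.07% | 14% | 69% |
| 0.9 | 40% | 0.02% | 12% | 95% |

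If each arm were compared only with its own baselines, the ratio would be 1 − ρ, that is 50% to 10%.

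**5En% versus 30En% at one visit.** The two cells hold different people, and the simulated error rate stays at its nominal level. Noncentrality is 1.213/√(2/16) = 3.43. With 61 degrees of freedom (64 observations, three cells) and level 0.0167, power is about 83%. Baseline as covariate multiplies the variance by 1 − ρ², so noncentrality is 3.43/√0.75 = 3.96 at ρ = 0.5 and 3.43/√0.51 = 4.80 at ρ = 0.7. Power is then about 91% and 98%. For a smaller effect of 0.5 SD at the same level, the planned test has about 16% at any ρ, against 19%, 29%, 43% and 73% with the covariate at ρ = 0.5, 0.7, 0.8 and 0.9.

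**Week 12 against week 1.** Suppose the ANOVA is run at each visit and the true effect is identical at both (0.7 to 1.2 SD, ρ = 0.7, 16 per arm). Significance at week 1 but not at week 12 then appears in about 8 to 12% of trials at the Bonferroni level, and each could be misread as a transient effect. A direct contrast has standard error σ√(4(1 − ρ)/n). At n = 16 this is 0.354, 0.274, 0.224 and 0.158 SD for the four values of ρ. Multiplying by 1.960 + 1.282 gives differences detectable with 90% power at 0.05 of 1.15, 0.89, 0.72 and 0.51 SD. Treating the visits as independent would give 0.5 × 3.242 = 1.62 SD.

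**Muscle protein synthesis.** Sections 3 and 6.3.2 place this measurement on one voluntary test day after the last chamber stay. No value exists before the diets begin, so the baseline comparison in section 8.2 cannot be run for it. The fasted sample on that day follows 12 weeks of diet and is not the 15En% baseline.

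**The case against.** **The main results are not invalid.** A reader might infer that every primary result carries the wrong error term. The documents do not support that. The randomised comparison of the two diets at one visit is between different people and keeps its type I error. It is only inefficient.

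**There is no excess of false positives.** With positive correlation the baseline contrasts reject too rarely. The harm is missed effects.

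**The power loss depends on the effect chosen.** Illustrations at 0.5 SD look dramatic. At the effect the protocol designs for, the loss is from about 91% or 98% to about 83%, and at 20 per arm the planned test itself reaches about 91%. The gap between the 91% behind the sample size and the 83% here comes from the Bonferroni level, not from the missing covariate.

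**The time question is not wholly ignored.** A between-diet result at week 12 bears on whether an effect is still present, and the objectives in section 2 do not use the words permanent or transient. This stands in part: what is missing is a formal test of change between the visits, and section 1 does state the aim.

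**The regression in section 8.2 lists no covariates and could include diet.** That is possible, but neither regression names baseline or visit, so neither closes the gap.

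**An analysis plan could supply the detail.** The protocol does not leave the method open. It names one-way ANOVA for the main outcomes and, in the next sentence, repeated measures for VAS ratings.

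**Conclusion.** The point holds in a bounded form. The diet-versus-baseline contrasts for energy expenditure, substrate oxidation and sleep rest on an independence assumption that the design makes false, and they are conservative as a result. The between-diet contrast is valid but gives up precision that the data already offer. No formal week-12-versus-week-1 comparison between diets is planned for any main outcome, and the baseline comparison stated for protein synthesis is impossible.

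The independence problem, the missing contrast and the missing baseline for protein synthesis follow from the text alone. The sizes depend on the assumed correlation and equal variances. Those for the baseline contrasts also depend on the inferred grouping of the baselines.

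**What to change.** In section 8.2, for energy expenditure, substrate oxidation and sleep:

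- Replace the one-way ANOVA with a repeated-measures or mixed model on the week 1 and week 12 values, with diet, visit, diet-by-visit, the baseline value of the outcome as covariate, and a subject effect.
- Prespecify the diet-by-visit contrast (week 12 minus week 1, 30En% against 5En%) as the test of permanence, with a 95% confidence interval. At this sample size a non-significant contrast would not by itself show that an effect lasts, so the interval matters.
- Test change from baseline within an arm with a paired, within-subject error term.

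For muscle protein synthesis, state a between-arm comparison only. Align section 8.3 so that its regressions are not taken to supply the baseline-adjusted diet effect.

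Which visit is primary and which further covariates enter are for the sponsor to decide. The cost is wording in sections 8.2 and 8.3. No new subjects or measurements are needed, and SPSS, the package already named, can fit these models.
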